## Abstract

**Background:**

The pp-Whipple procedure requires extensive preparation. The conventional preparation technique is done with scissors for dissection and ligatures, and with clips and sutures for hemostasis. This procedure is very time-consuming and requires numerous changes of instruments. The LigaSure™ device allows dissection and hemostasis for preparation with one instrument. Up to now there has been no comparison of the two techniques with regard to operating time and the patients' outcome. It is still unclear which technique has the optimal benefit/risk ratio for the patient.

**Methods/Design:**

A single-center, randomized, single-blinded, controlled superiority trial to compare two different techniques for dissection in a pp-Whipple procedure. 102 patients will be included and randomized pre-operatively. All patients aged 18 years or older scheduled for primary elective pp-Whipple procedure who signed the informed consent will be included. The primary endpoint is the operating time of the randomized technique. Control Intervention: Conventional dissection technique; experimental intervention: LigaSureTM dissection technique. Duration of study: Approximately 15 months; follow up time: 3 years. The trial is registered at German ClinicalTrials Register (DRKS00000166).

## Background

The procedure was originally described by Alessandro Codivilla in 1898, A.O. Whipple improved it in 1935. The Whipple procedure is the standard method for therapy of cancerous tumours, inflammation and stenosis near the head of the pancreas. In the classic Whipple-procedure (c-Whipple) the head of the pancreas, the duodenum, the regional lymph nodes, the gastric antrum, the gallbladder, and the distal bile duct are removed. The pylorus-preserving-Whipple procedure (pp-Whipple) was established by Traverso and Longmire in 1978. During this procedure the gastric antrum is not removed. In recent years the pp-Whipple procedure is preferred because several studies have shown that the classic Whipple procedure is not superior to the pp-Whipple procedure regarding the oncological outcome or peri- and postoperative complication rates [1-5].

About 300 patients are operated on following the pp-Whipple procedure at the department each year. As the pancreas is fed by many vessels [6], it is necessary to use lots of ligatures, clips and sutures for hemostasis after dissection. This dissection technique is very time-consuming and requires numerous changes of instruments. The use of high-frequency feedback-controlled electrothermal bipolar vessel sealant technology, known as the LigaSure™ Vessel Sealing System (LVSS), is a new alternative for dissection and hemostasis. The bipolar vessel dissection devices require no change of instruments for dissection and hemostasis [7-10]. The current is provided by a special HF-generator and contains a very high capacity with a low voltage. The body's proteins, such as collagen and elastin, are converted so a permanently sealed zone results. As only the tissue between the branches is sealed, lateral thermic tissue damages can be limited to a minimum. Several authors describe a tendency of reduced intraoperative blood loss and transfused blood preservations [11-13]. Other trials show reduced operating time using the LVSS in several surgical procedures, such as thyroid, gynecology, urology and haemorrhoidectomy surgery [9,11,13,14].

Correct dissection in the operation field is very important to avert secondary bleeding or other complications, which might cause re-operation or elevate the patients' morbidity and mortality [15].

## Methods/Design

### Aim of study

The comparison of LVSS versus conventional dissection technique in pylorus-preserving pancreatoduodenectomy regarding operation time and complication rates.

### Number of patients needed

The sample size calculation is based on a two sided t-test for differences with respect to the primary endpoint. The data evaluation and comparison of seven patients operated on with the LVSS versus seven patients operated on with the conventional dissection technique showed a reduction of operating time of 40 minutes in the LVSS group. An evaluation of all pp-Whipple operations in 2010 (138 operations) showed a mean operating time of 300 min with a standard deviation of 66 minutes. If the difference in operating time is 40 minutes, there will be an 80% (1-β) chance that a trial involving 88 patients (44 per group) could detect a significant difference at an alpha level of 5%s (SAS 9.1 proc power). To compensate possible drop outs 14 patients (15%) more will be randomized. Therefore 102 patients (51 per group) will be included (Figure 1).

**Figure 1 F1:**
[figure not shown]
**Flowchart according to CONSORT**.

A minimum time saving of 40 minutes would be needed to change the manner of surgical preparation towards the use of the LigaSure™ because of the high costs of this device. A basic configuration for the use of the LigaSure™ device costs nearly € 30.000, additionally € 260 per patient are the costs for the single use device itself. The pilot trial with 14 patients by Gehrig et al. showed a cost reduction of nearly € 800 per patient for a operative time saving of 40 minutes (€ 500 for 30 minutes). Therefore we believe a time saving of at least 40 min would be needed to convince surgeons and hospital managers to consider the purchase and use of this equipment on a rugulary basis.

### Eligibility

#### Inclusion criteria

• Clinical suspicion of a cancerous tumour on the head of the pancreas, relied on imaging and laboratory values

• Aged 18 years or older

• Patients scheduled for primary pp-Whipple procedure

• Informed consent

#### Exclusion criteria

• Participation in another trial with interference of outcome of this study

• Lack of compliance (assessed by the trial investigator)

• Impaired mental state or language problems (patient is not able to read German)

#### Subject withdrawal criteria

• At their own request or at request of the legal representative

• If, in the investigator's opinion (surgeon who performs the dissection), continuation of the trial would be detrimental to the subject's well-being (e.g. bleeding or other independent acute health problems)

All withdrawn patients will be reported in the final results to guarantee maximum transparency.

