### Randomization and procedures for minimizing bias

#### Minimizing systemic bias

To achieve comparable groups for known and unknown risk factors randomization will be performed as unstratified block randomization with random block sizes in a 1:1 allocation ratio. Allocation to treatment group will be carried out by the randomization software RITA^® ^[17]. Randomization numbers that become vacant by withdrawal will be reused.

102 patients will be recruited according to the sample size calculation. Randomization will be performed independently by a study nurse of the Clinical Study Center Surgery (KSC) to the conventional group or to the LVSS group. Randomization will be carried out after patient has signed the informed consent and will be documented in the case report file of every patient. Intervention will be scheduled 1-3 days after inclusion depending on the earliest operation appointment possible.

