#### Minimizing measurement bias

A study nurse will document and monitor the procedure in the operating theatre. The patients are blinded for the used operation technique. Physicians' blinding is not possible due to the different techniques used during the operation.

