#### Secondary endpoints

• Perioperative complications:

○ Intraoperative Bleeding

○ Perforation of hollow organs (stomach, small intestine, colon, gallbladder/biliary tract)

○ Lesion in parenchymatous abdominal viscus (liver, spleen, pancreas)

• Postoperative complications:

○ Secondary bleeding/hematoma

○ Wound infection

○ Gastroparesis

○ Postoperative pancreatic fistula (POPF)

○ Intraabdominal abscess

○ Anastomotic leakage of the choledochojejunostomy

○ Anastomotic leakage of the gastrojejunostomy

• Re-intervention (operational/interventional)

• Intraoperative blood loss

• Hospital stay

• Re-hospitalization-rate (30 days postoperative)

• Duration of anesthesia

• Intraoperative material consumption

• Material costs, calculated by the material consumption

• Overall costs of the operation, calculated by the indirect and direct costs during the hospital stay and the costs accumulated 30 days postoperatively

• Local recurrence of disease

• Quality of life analysed in questionnaires (EORTC QLQ-C30, EORTC QLQ PAN26, special questionnaire of the European Pancreas Center, University of Heidelberg)

• Mortality rate

Definitions of secondary endpoints are shown in Table 2.

**Table 2 T2:** Definition of secondary endpoints

Perioperative complications	Complication	Definition
Bleeding	Severe intraoperative bleeding	Mentioned in operation report

Perforation of hollow organs	Perforation of stomach, small intestine, colon or biliary tract/gallbladder	Mentioned in operation report

Lesion in parenchymatous abdominal viscus	Lesion in liver, spleen, pancreas	Mentioned in operation report

Postoperative complications	Complication	Definition

Secondary bleeding/hematoma	postoperative bleeding	Need for more than 2 units of red blood cells within 24 hours after surgery OR Need of surgical treatment (mentioned in re-operation report)
	
	Hemtoma	Radiological (ultrasound, CT) findings positive for reoperation or reopening of the wound

wound infection		Deep and/or superficial according to CDC definition [20]

Gastroparesis	delayed gastric emptying (DGE)	Consensus definition of delayed gastric emptying after pancreatic surgery of the International Study Group of Pancreatic Surgery (ISGPS) [21]

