pp-Whipple specific complications	postoperative pancreatic fistula (POPF)	Drain output of any measurable volume of fluid on or after postoperative day 3 with an amylase content greater than 3 times the serum amylase activity. Three different grades of POPF (grades A, B, C) are defined according to the clinical impact on the patient's hospital course [22]
	
	Intraabdominal abscess	Intraabdominal collection of purulent or infected fluids (positiv bacterial culture) requiring radiological (puncture or drainage of purulent fluid) or surgical intervention (re-operation)
	
	anastomotic leakage of choledochojejunostomy	Bilirubin-rich (more than 5000 units) drainage fluid of more than 50 ml per day on or after the 10th postoperative day OR Mentioned in re-operation report
	
	anastomotic leakage of gastrojejunostomy	Radiological findings correlating to gastrojejunostomy insufficiency (e.g. CT with contrast medium withdrawal) OR Mentioned in re-operation report

Further secondary endpoints		Definition

Re-intervention	operational	Reoperation due to any cause

	interventional	Interventional haemostasis or drainages due to any cause

Intraoperative blood loss		Mentioned in operation report

Hospital stay		Time of admission to discharge

Re-hospitalization-rate		Re- hospilization within 30 days after surgery due to any cause

Duration of anesthesia		Mentioned in anesthesia report

Intraoperative material consumption		All materials, which are necessary for surgery

Material costs		Costs, which occurs due to the material consumption during the surgery

Overall costs		Costs include expenditure for personnel and use of operating room as well as for material consumption

Local recurrence of disease		Radiological (ultrasound, CT) findings positive for recurrence of disease

Quality of life		EORTC QLQ-C30, EORTC QLQ PAN26 and special questionnaire of the European Pancreas Center Heidelberg on day 30 (±10days), 90 (±10 days), 180 (±10 days), 1 year (± 1 month), 1,5 years (± 1 month), 2 years (± 1 month), 2,5 years (± 1 month) and 3 years (± 1 month)

Mortality rate		Death to any course until year 3 after operation

Assessment:

1. Perioperative complications of the pp-Whipple procedure will be recorded on the day of operation by an independent study nurse.

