2. Postoperative complications of the pp-Whipple procedure will be recorded in patients' discharge data and on visit 1 (30 days after operation) after a standardized telephone interview by a study nurse. A confirmation by the patient's family physician will be requested following any abnormality reported by the patient. The following standard aftercare takes place initially twice quarterly (visit 2, 3 months after operation; visit 3, 6 months after operation) then half-yearly for two years (visit 4, 12 months after operation; visit 5, 18 months after operation; visit 6, 24 months after operation; visit 7, 30 months after operation and visit 8, 36 months after operation) with a clinical examination, imaging (ultrasound, CT, MRT), general and standardized questionnaires (EORTC-QLQ-C30, EORTC-QLQ-PAN26 and a special questionnaire from the European Pancreas Center) and laboratory value control in the European Pancreas Center at the surgical department.

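### The unblinded surgeon may withdraw a patient from the trial for bleeding, itself a secondary endpoint, so that patient's later outcomes may be lost

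*Protocol article*

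**What the plan says.** All references are to the protocol article.

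- **Subject withdrawal criteria.** Besides withdrawal at the patient's or legal representative's request, a patient may be withdrawn if the surgeon who performs the dissection judges that "continuation of the trial would be detrimental to the subject's well-being (e.g. bleeding or other independent acute health problems" applies. On what happens next, this section says only: "All withdrawn patients will be reported in the final results to guarantee maximum transparency".
- **Minimizing systemic bias.** "Randomization numbers that become vacant by withdrawal will be reused". Nothing limits this to withdrawal before surgery.
- **Minimizing measurement bias.** "Physicians' blinding is not possible due to the different techniques used during the operation".
- **Secondary endpoints.** The first perioperative complication listed is "Intraoperative Bleeding", which Table 2 defines as severe bleeding mentioned in the operation report. Secondary bleeding heads the postoperative list.
- **Assessment of secondary endpoints.** "Perioperative complications of the pp-Whipple procedure will be recorded on the day of operation by an independent study nurse". For later events, "Postoperative complications of the pp-Whipple procedure will be recorded in patients' discharge data and on visit 1", the day-30 telephone interview; visits 2 to 8 then run to 36 months. Table 2 defines mortality as "Death to any course until year 3 after operation".
- **Analysis.** The primary comparison covers randomized patients who had the pp-Whipple operation, analysed as randomized, with an additional per-protocol analysis. Secondary endpoints are descriptive.

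**The concern.** Two decisions are merged into one. Abandoning the allocated dissection technique in a patient who is bleeding is a clinical safety decision, and the surgeon must be free to take it. Leaving the trial is different: after the operation the trial consists of a telephone call and follow-up visits, and observing a patient who has bled cannot harm that patient.

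As worded, the rule ends trial participation. The named trigger is an outcome under comparison, and the person who decides knows the arm. If follow-up stops on withdrawal, the patients removed are selected by an outcome that the technique may influence and by an unblinded judgement. The Aim of study section sets complication rates beside operating time, so the safety half of the aim is exposed.

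**Working it through.** **Which data are at risk**

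| Outcome | When recorded | Effect of withdrawal for bleeding |
|---|---|---|
| Operating time | Day of operation | Probably kept: the primary comparison covers all who had the operation, as randomized |
| Intraoperative bleeding, perforation, organ lesion | Operation report; study nurse the same day | Probably kept |
| Postoperative complications | Discharge data, day-30 interview, later visits | May be lost |
| Re-intervention, re-hospitalization | Day-30 interview, later visits | May be lost |
| Quality of life, recurrence, three-year mortality | Visits up to 36 months | May be lost |

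The article does not say that collection stops. It states a withdrawal rule without saying that collection continues, and reuse of vacated numbers suggests replacement rather than retention. The only missing-data rules it gives are for quality of life, and there a patient with no measurement after surgery is left out of the analysis.

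**Arm size.** Number of patients needed gives 44 per group for 40 minutes, SD 66, two-sided 5% and 80% power. The exact t-test gives 80.3% at 44 per group, so this reproduces. With the 14 extra patients, 88 + 14 = 102, or n = 51 per arm.

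**Size of the possible bias.** The article gives no withdrawal, bleeding or complication rates, so these inputs are assumptions:

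- withdrawn for bleeding: wL in the LVSS arm and wC in the conventional arm, each 0 to 5 of 51;
- a later binary event, such as re-intervention, has rate p in retained patients of an arm and p + e in withdrawn ones, with e from 10 to 50 percentage points and the same in both arms.

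The observed rate in an arm is p. The true rate is p + (w/51) × e. Hence, for LVSS minus conventional:

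bias = observed difference − true difference = −[(wL − wC)/51] × e

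| wL | wC | e (points) | Bias (points) |
|---|---|---|---|
| 3 | 0 | 10 | −(3/51) × 10 = −0.6 |
| 3 | 0 | 30 | −1.8 |
| 3 | 0 | 50 | −2.9 |
| 3 | 1 | 30 | −(2/51) × 30 = −1.2 |
| 3 | 3 | any | 0 |
| 0 | 3 | 30 | +1.8 |
| 5 | 0 | 50 | −(5/51) × 50 = −4.9 |
| 0 | 5 | 50 | +4.9 |

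The arm with more withdrawals looks better than it is.

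**Uncertainty without imbalance.** If the lost patients' outcomes are unknown, the gap between the extreme assignments (all events in one arm's lost patients and none in the other's, then the reverse) is (wL + wC)/51. With 3 lost per arm this is 6/51 = 11.8 points, even though the bias under the model above is zero.

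**The case against.** The strongest reply has five parts.

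1. **The harm is inferred from silence.** A journal article may leave follow-up after withdrawal to the full protocol. Silence alone would indeed be no finding. Here, though, the article states the rule, the decision-maker and the example, and as worded it permits exit because of an outcome.
2. **The word independent.** Bleeding may be meant as a problem unrelated to the dissection. That reading is open. It does not rescue the rule, because bleeding during dissection cannot reliably be judged unrelated to the dissection technique, and the decision lies with the unblinded operator.
3. **Other safeguards.** Analysis as randomized, with a separate per-protocol analysis, keeps technique deviations in the main analysis. Withdrawn patients are reported, the trial coordinator cross-checks adverse events, and visits 2 to 8 are described as standard aftercare. These make total loss less likely. But analysis as randomized cannot restore data never collected, reporting a withdrawal is not follow-up, and routine aftercare does not mean trial data are recorded after withdrawal.
4. **Number reuse.** A vacant number may simply be one whose allocation was never used. This stands as a possibility, so the sentence is supporting evidence and not proof.
5. **Size.** Assuming a 20% event rate, the 95% half-width for a difference with 51 per arm is 1.96 × √(2 × 0.16/51) = 15.5 points, well above the biases shown. Secondary p-values carry no confirmatory weight. Both points are right and limit the seriousness; neither is a reason to keep an avoidable, outcome-dependent loss.

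**Conclusion.** The concern holds. An unblinded surgeon may end a patient's participation because of an event that the trial compares, and nothing in the article secures that patient's later outcomes. The descriptive safety comparison can therefore be biased. On the stated assumptions (0 to 5 withdrawals per arm, an excess of 10 to 50 points, equal in both arms) the bias lies between zero and 4.9 points in either direction; 3 lost per arm leaves an 11.8-point span even without bias. The actual size and direction cannot be derived from the document.

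Operating time, the same-day bleeding record and the confirmatory test are largely unaffected. The wording should be fixed because complication rates are part of the stated aim and the correction is cheap.

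**What to change.** Under Subject withdrawal criteria, replace the second criterion with three statements and remove bleeding as a ground for leaving the trial:

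1. The surgeon may stop the allocated technique at any time for the patient's safety. The time, the reason and the technique used afterwards are recorded.
2. Stopping the technique is not withdrawal. The patient stays in the randomized arm; skin-to-skin time, all perioperative and postoperative endpoints, serious adverse events and visits 1 to 8 are still collected and analysed as randomized.
3. Only withdrawal of consent by the patient or legal representative ends follow-up.

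Under Minimizing systemic bias, add that a randomization number is not reused once surgery has begun.

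The cost is a short rewording in two sections and one case report form field for a technique switch. It needs no extra visits, because visits 2 to 8 are already standard aftercare, and it does not restrict the surgeon. The one downside is that results which include technique failures may look less favourable.

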### Consent

The DISSECT- Trial will be conducted in accordance with the protocol and in compliance with the moral, ethical, and scientific principles governing clinical research as set out in the Declaration of Helsinki 1989 [16] and Good Clinical Practice (http://www.ema.europa.eu/docs/en_GB/document_library/Scientific_guideline/2009/09/WC500002874.pdf). The protocol was approved by the Ethics Committee of the University of Heidelberg (S-061/2009). All Patients who are assigned the pp-Whipple procedure at the Department of General, Abdominal and Transplant Surgery, University of Heidelberg, will be screened for eligibility and informed about the DISSECT trial during a visit prior to treatment. The study procedure, risks, benefits and data management will be clarified in detail before the patients are asked to give their informed consent. After inclusion of the patient in the study, his personal data (height (cm), weight (kg), gender, Karnowsky-Index (0 - 100%), medication of immunsuppression, antibiotics (yes/no), chemotherapy (yes/no)) will be recorded into the CRF. (Table 1)

**Table 1 T1:** Study Visit Schedule

			Follow-up	Follow-up
			
	Day of screening	Day of operation	Visit 1 (day 30post OP ) by phone	Visit 2-8 (European Pancreas Center)
Past medical history*	X			

Informed consent	X			

Personal data**	X			

**Examination of primary endpoints**:				
Operating time		X		

**Examination of primary endpoints**:				
Mortality		X	X	X
Peri- and postoperative complications		X	X	X
Re-intervention			X	X
Intraoperative blood loss		X		
Hospital stay			X	
Reuptake			X	X
Time of anesthesia pre- and postoperative		X		
Intraoperative material consumption		X		
Local recurrence				X
Quality of life	X			X

Safety criteria AE, SAE (2.6)		X	X	X

* study-relevant past medical history, past surgical history

** height (cm), weight (kg), gender, Karnowsky-Index, medication of immunsuppresion, antibiotics, chemotherapy

### Randomization and procedures for minimizing bias

#### Minimizing systemic bias

To achieve comparable groups for known and unknown risk factors randomization will be performed as unstratified block randomization with random block sizes in a 1:1 allocation ratio. Allocation to treatment group will be carried out by the randomization software RITA^® ^[17]. Randomization numbers that become vacant by withdrawal will be reused.

102 patients will be recruited according to the sample size calculation. Randomization will be performed independently by a study nurse of the Clinical Study Center Surgery (KSC) to the conventional group or to the LVSS group. Randomization will be carried out after patient has signed the informed consent and will be documented in the case report file of every patient. Intervention will be scheduled 1-3 days after inclusion depending on the earliest operation appointment possible.

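### Reissuing randomization numbers vacated by withdrawal can make the replacement patient's arm foreseeable, and it leaves unclear whether withdrawn patients are still analysed

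*Protocol article*

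**What the plan says.** The protocol article (Minimizing systemic bias) specifies "unstratified block randomization with random block sizes in a 1:1 allocation ratio", run in randomization software by a study nurse after consent, with the allocation documented in each patient's case report file. Surgery follows within days: "Intervention will be scheduled 1-3 days after inclusion depending on the earliest operation appointment possible". The same section then rules: "Randomization numbers that become vacant by withdrawal will be reused". Nothing limits this to patients withdrawn before their arm is disclosed, and nothing says that a fresh allocation is drawn.

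Four other places bear on it:

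- **Minimizing measurement bias:** "Physicians' blinding is not possible due to the different techniques used during the operation". Patients are blinded.
- **Subject withdrawal criteria:** besides the patient's own request, withdrawal is possible if "in the investigator's opinion (surgeon who performs the dissection), continuation of the trial would be detrimental to the subject's well-being". Bleeding is a named example. Withdrawn patients are to be reported in the final results.
- **Analysis:** the primary comparison covers all randomized patients who underwent surgery involving the pp-Whipple procedure, analysed as randomized under the intention-to-treat principle.
- **Number of patients needed:** "To compensate possible drop outs 14 patients (15%) more will be randomized", which raises 88 to 102.

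**The concern.** There are two separate problems.

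**Concealment.** Random block sizes exist so that nobody can work out the next assignment. A reissued number gives that away if it keeps its arm, which is the natural meaning of reusing a number. The surgeon who treated the withdrawn patient knows the arm, and so does the nurse who randomized that patient. Whoever can tell that this number is to be issued can foresee the arm and could, in principle, influence which patient receives it.

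**Status of the withdrawn patient.** Calling the number vacant implies that the patient's place in the trial is empty. The Analysis section implies the contrary for anyone who had the procedure. The promise to report withdrawn patients does not settle it, because reporting is not analysis. This matters because an unblinded operator may withdraw a patient for bleeding. Bleeding is itself a secondary endpoint and plausibly lengthens the operation, which is the primary endpoint.

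**Working it through.** **1. The plan's own sample size.** Inputs from Number of patients needed: difference 40 min, SD 66 min, two-sided alpha 5%, power 80%. The standardized difference is 40/66 = 0.606. The noncentral t calculation gives 43.7, so 44 per arm and 88 in total, with power 80.3%. The stated figure is reproduced.

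**2. Is reuse needed for power?** No. If all 14 extra patients are lost, 102 - 14 = 88 remain, and power is 80.3%. The margin covers a loss of 14/102 = 13.7%.

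**3. How many allocations could be foreseeable?** The document gives no withdrawal rate. If every one of the 14 budgeted drop-outs vacated a number and all were reissued, 14 of 102 numbers (13.7%) would be affected. With no withdrawals, none would be.

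**4. What 102 then counts.** If 102 means filled numbers, the patients randomized are 102/(1 - w) for withdrawal rate w (assumed values):

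| w | 102/(1 - w) |
|---|---|
| 5% | 107 |
| 10% | 113 |
| 15% | 120 |

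**5. Does reuse itself bias operating time?** Assume no true difference, a share p of patients who bleed, and d extra minutes when they do. An arm analysed in full has mean m + p·d. An arm from which all bleeding patients are removed has mean m. The spurious difference is p·d, whether or not non-bleeding replacements fill the gaps. The values of p and d below are assumptions; neither is in the document. Simulation with 51 per arm and total SD 66 gave:

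| Handling of bleeding patients | p = 10%, d = 60 | p = 15%, d = 90 |
|---|---|---|
| LVSS arm only, withdrawn, replaced, not analysed | bias 6.0 min, type I error 7.5% | 13.5 min, about 19% |
| LVSS arm only, withdrawn, not replaced, not analysed | 6.0 min, 7-8% | 13.5 min, 17-18% |
| Withdrawn and not analysed in both arms alike | about 0, about 5% | about 0, about 5% |
| Kept in the analysis, replacements added | about 0, about 5% | about 0, about 5% |

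The first two rows agree with p·d: 0.10 × 60 = 6 and 0.15 × 90 = 13.5. The bias comes from one-sided exclusion from the analysis. Reissuing the number adds almost nothing to it.

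**6. Cost of not reusing numbers.** With 88 evaluable patients split n1 and n2, efficiency relative to 44/44 is 4·n1·n2/88². For 46/42 this is 7728/7744 = 99.8%; for 48/40 it is 7680/7744 = 99.2%.

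**The case against.** The best defence is that the Analysis section already answers the second problem. A patient withdrawn for bleeding during a completed pp-Whipple operation belongs to the stated analysis set, operating time is in the operation log, and withdrawn patients are promised a place in the report. That stands, and it removes any claim to a fixed size of bias. What it does not do is explain why such a patient's number should count as vacant.

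A reader might draw four stronger conclusions. The document does not support them.

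- **That the LVSS arm sheds its long operations, with a bias of 6 to 13 min.** This needs withdrawn patients to be left out of the analysis, contrary to the Analysis section, and in one arm only. The withdrawal criterion applies to both arms. The LVSS description already provides for ligating larger vessels, so ligation as such is no departure from the allocated technique.
- **That the next patient's arm is always known.** This arises only after a number has been vacated, and only if the number keeps its arm and those involved know when it is reissued. The article does not describe how the software handles this.
- **That two patients under one number contradict intention to treat.** If the number keeps its arm, both patients have the same assigned arm and each can be analysed in it. Sharing a number is a traceability problem.
- **That replacement on top of a drop-out margin is an error.** It is redundant, but conservative for power: 51 analysed per arm would give 85.8%.

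**Conclusion.** The point holds in a limited form. The reuse rule is stated without qualification and can make the allocation of reissued numbers foreseeable. It brings no power that the plan needs. This rests on a number keeping its arm when reused, and on the surgeon or nurse knowing that arm, which the unblinded design makes likely. The extent is between none and about 14% of numbers, depending on a withdrawal rate that the document does not give.

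The withdrawal, randomization and analysis sections also do not fit together on whether a surgeon-withdrawn patient is analysed. Outcome-related bias is possible only if such patients are not analysed and withdrawal differs between the arms. The minutes and error rates in the table illustrate that condition and are not an estimate for this trial. The concealment problem is the firmer of the two: it does not depend on how the analysis treats withdrawn patients and cannot be repaired afterwards.

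**What to change.** Replace the sentence under Minimizing systemic bias with: *Randomization numbers are never reissued; a withdrawn patient keeps the number and arm, and the next patient receives the next unused allocation.*

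Reconcile Subject withdrawal criteria and Minimizing systemic bias with Analysis by stating that patients withdrawn by the surgeon after randomization who underwent the pp-Whipple procedure stay in the intention-to-treat analysis in their randomized arm, with operating time taken from the operation log where consent allows. This concerns data and analysis only and leaves the surgeon's decisions in theatre untouched.

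State that 102 counts randomized patients, and rely on the 14-patient margin for losses.

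The cost is a short amendment and a setting in the randomization software, with no added patients. The arms may end slightly unequal; even a 48/40 split keeps 99.2% of the efficiency of equal arms.
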